### Data collection

The DN will record the result of ETCO_2_ detection (i.e., presence of any capnographic waveform and ETCO_2_ value and the number of index tests performed per participant) and follow up with the X-ray and the pH test results; and location of NGT (stomach, esophagus, or tracheobronchial tree). These results will be recorded on the data collection form.

The DN will also collect participants’ demographic and clinical data (S1 File), including age, gender, setting (ward/unit and type of hospitals), principal medical diagnosis, reasons for current AED visit or hospitalisation, past medical and surgical history, level of consciousness (assess using Glasgow Coma Scale), level of fitness or frailty (assess using Clinical Frailty Scale), respiration status and support, indication for NGT insertion, type of NGT, mode, amount and frequency of enteral feeding, type of diet or enteral formula, fluid and food intake within 6 hours before NGT insertion, medications administered within 12 hours of NGT insertion, results and duration of the index test and reference test/s performed, complications or adverse events associated with insertion and the testing (index test and reference test/s), cost of the index test, and cost of the reference test/s used.

### Study duration

The duration of the research will be two years, and data collection will begin in July 2023.

## Data analysis

The sample size is determined to give the study adequate precision to estimate the sensitivity and specificity of using capnography in detecting the placement of NGTs using the reference standards of measurement of radiography and aspirates for pH value. In anticipation of sensitivity and specificity of values greater than 90% [17], a sample size of at least 500 participants would be sufficient to estimate these parameters with a margin of error of at most ±3% at a significance level of 0.05. The sample size calculation was performed using PASS 16 (NCSS, Kaysville, USA). Eligible participants will be evenly recruited from the 39 participating wards/units. The target sample size will therefore be rounded up to 507 with 13 eligible participants per each of the 39 wards/units.

IBM SPSS 26.0 (IBM Crop., Armonk, NY) will be used to conduct the data analysis. Participants’ demographic and clinical characteristics will be presented by appropriate descriptive statistics, including mean ± standard deviation, median (inter-quartile range), and percentages for normally distributed, skewed continuous, and categorical variables respectively. Any cases with missing data on the index test or the reference standard results will be excluded from the test accuracy analysis. The true positives (i.e., NGT placements that are tested positive by both index test and reference test/s), false negatives (i.e., NGT placements that are tested negative by index test but positive by reference test/s), true negatives (i.e., NGT placements that are tested negative by both index test and reference test/s), and false positives (i.e., NGT placements that are tested positive by index test but negative by reference test/s) will be calculated, based on which the sensitivity, specificity, positive predictive value, and negative predictive value of the capnography test will be calculated with reference to a combination of X-ray and aspirate pH test using the following formulas:

$$\text{Sensitivity}:\;\text{True}\;\text{Positive}/\left(\text{True}\;\text{Positive}+\text{False}\;\text{Negative}\right)\times 100\%$$

$$\text{Specificity}:\text{True}\;\text{Negative}/\left(\text{True}\;\text{Negative}+\text{False}\;\text{Positive}\right)\times 100\%$$

$$\text{Positive}\;\text{Predictive}\;\text{Value}:\text{True}\;\text{Positive}/\left(\text{True}\;\text{Positive}+\text{False}\;\text{Positive}\right)\times 100\%$$

$$\text{Negative}\;\text{Predictive}\;\text{Value}:\text{True}\;\text{Negative}/\left(\text{True}\;\text{Negative}+\text{False}\;\text{Negative}\right)\times 100\%.$$

The Area Under the Receiver Operating Characteristic Curve (AUC) of capnography will be calculated to assess the overall diagnostic performance of capnography. The test accuracy level is considered high when the AUC value is ≥ 0.9 [25].

The variability in diagnostic accuracy in participants from different age groups, gender, level of consciousness, level of frailty, type of illness, respiration status and support, drug use, fluid or food intake, types of hospitals and units will be explored by using chi-squared or Fisher’s exact tests, as appropriate. The time spent and the cost of the index test (capnography monitoring) and the reference tests (radiography and aspirate pH test) will be compared using the paired t-test. All statistical tests are 2-sided with level of significance set at 0.05. All cost data will be expressed in Hong Kong and US dollars and the procedural time will be expressed in hours and minutes.

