**Materials and methods:**

A prospective observational diagnostic study will be conducted. Patients ≥ 18-year-old and requiring the insertion of an NGT will be recruited using a convenience sampling method from 39 general medical and geriatric wards, intensive care units, accident and emergency departments, and subacute/rehabilitation/infirmary wards in 21 acute or subacute/convalescent/extended care hospitals. ETCO_2_ detection by sidestream capnography, which indicates an airway intubation of an NGT when a capnogram waveform or an ETCO_2_ level > 10mmHg (1.33 kPa) occurs, will serve as the index test. The reference standards will be the X-ray performed and pH value of gastric aspiration (pH ≤ 5.5) after the index test. Each participant will be included only once. Sensitivity, specificity, positive predictive value, negative predictive value, and area under the receiver operating characteristic curve of capnography will be calculated to assess the diagnostic performance of capnography. The variability in diagnostic accuracy in participants with different characteristics will be explored by using chi-squared or Fisher’s exact tests. The time spent and the cost of the tests will be compared using the paired t-test. All statistical tests will be two-sided with a level of significance set at 0.05.

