## Introduction

Nasogastric tube (NGT) placement is a common practice in hospital settings for assessment, nutrition support, and administration of medication [1,2]. Unfortunately, misplacement of NGTs is common, with an estimated 60% of misplacements resulting in detrimental effects [3,4]. In fact, in over 80% of these misplacements the NGTs were placed in the respiratory tract, leading to serious pulmonary complications, including aspiration pneumonia or respiratory failure [4,5]. Chest/abdominal X-ray is the gold standard for verifying correct NGT placement in the stomach. However, radiography is not always available conveniently at the bedside [6]. Other methods for verifying NGT placement include biochemical measurements of aspirates for pH value or presence of bilirubin, trypsin or pepsin, spring gauge pressure manometer, magnetic detection, ultrasonography, auscultation, and visual inspection of aspirates [7–11]. Factors often compromised the accuracy of these methods include the inability to aspirate adequate fluids for testing, difficulty in visually differentiating the colour change in test strips, use of antacids, reflux of gastric contents, or patients with altered level of consciousness [7,8,11]. Therefore, a reliable and effective bedside test to verify NGT placement is required.

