#### Reference standard

The reference standard is the test, series of tests, or set of procedures used to determine the presence or absence of the target condition in individuals, which in this study is airway intubation of an NGT [25]. This study will use radiography (chest/abdominal X-ray) as the reference standard for determining the correct placement of NGTs. Radiology will be performed as soon as possible and interpreted by a physician. A repeat radiography will be performed if necessary. We will also use pH-Fix-4.5–10 to determine the pH value, and its accuracy is +/- 0.2 with minimum increments of 0.5. A pH of 5.5 or below indicates gastric placement [2].

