**Fig 1 pone.0292667.g001:**
[figure not shown]
The flow of participants and data collection procedures in the study. This is the Fig 1 legend. (Abbreviation: DNs: Designated nurse(s) of the study venues; ETCO_2_: End-tidal carbon dioxide; ID: Identity; NGT: Nasogastric tube).

Ward nurses in the study site responsible for insertion of the NGT will estimate the distance to placement using the nose-earlobe-xiphoid (NEX) measurement and then insert the NGT according to the standard clinical practice guideline of the Hospital Authority Hong Kong (without connecting the capnography device at this point). The NGT used in all cases will be either a large bore NGT or a fine bore NGT. When the tube is advanced to a distance determined by the NEX method, ward nurses will inject and draw air with a 20 or 60 mL irrigation syringe to ensure tube patency and check if the NGT is not coiled inside the oral cavity.

Afterward, the DN will perform the index test (monitoring the ETCO_2_ using the capnography device) independently in the absence of the nurse who inserted the NGT in the following manner: i) Connect a new 20 or 60 mL syringe to the NGT and flush in 10 mL of air to clear any blockage; ii) Remove the syringe, connect the capnography device to the distal end of the NGT (by firmly connecting the device, the filter line with adapter and the NGT); iii) Check for any capnographic waveform and ETCO_2_ reading after a minimum of six breaths or one minute, whichever is longer, and record the results. To minimise bias in the study, the DN will not disclose the results of ETCO_2_ detection to the related ward nurses, participants, radiographer, or the physicians/radiologists who will interpret the X-ray imaging.

The ward nurses will independently aspirate gastric contents for pH measurement and report the pH value to the DN for record. The procedure will be stopped immediately if participants show signs of respiratory intolerance, such as repeated vigorous cough or cyanosis [26]. Then the patient will be arranged to receive a chest/abdominal X-ray. The DN will trace the X-ray results, which will then be interpreted by a physician (blind to the result of the index test) to confirm the position of the NGT. Enteral feeding (if prescribed) will begin once the position of the NGT is confirmed, otherwise, the NGT will be withdrawn and re-inserted according to the protocol.

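### Read literally, the missing-data rule drops a tube that has a capnography result and a readable X-ray but no aspirate; if aspirates fail more often in airway placements, this loses scarce airway cases and biases PPV down and NPV up

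*Protocol article*

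**What the plan says.** The exclusion rule is in the Data analysis section: "Any cases with missing data on the index test or the reference standard results will be excluded from the test accuracy analysis". What counts as the reference result is described in three ways.

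- **Data analysis:** sensitivity, specificity, PPV and NPV are calculated "with reference to a combination of X-ray and aspirate pH test". No rule for combining the two is given. The four cells of the 2×2 table are defined by a looser phrase that allows one or more reference tests.
- **Abstract (Materials and methods):** "The reference standards will be the X-ray performed and pH value of gastric aspiration (pH ≤ 5.5) after the index test".
- **Reference standard section:** "This study will use radiography (chest/abdominal X-ray) as the reference standard for determining the correct placement of NGTs". The use of pH is then added. The target condition is also fixed here, "which in this study is airway intubation of an NGT".

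On the ways a result could go missing, the Introduction lists "the inability to aspirate adequate fluids for testing" among the known weaknesses of bedside methods. The Procedures section (text following Fig 1) says "The procedure will be stopped immediately if participants show signs of respiratory intolerance, such as repeated vigorous cough or cyanosis", and its next sentence reads "Then the patient will be arranged to receive a chest/abdominal X-ray". The Data collection section records tube location as stomach, esophagus or tracheobronchial tree.

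**The concern.** If the reference result is X-ray and pH together, a tube that yields no fluid has an incomplete reference result, and the rule removes it. Such a case could have been classified: the target condition is airway placement, the X-ray shows location, and location is already on the data collection form.

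The loss matters most if it is uneven. The pH step aims to draw gastric contents, and a tube in the airway does not reach the stomach, so a failed aspirate is plausibly more common there. Airway placements are also the whole denominator of sensitivity. Losing them at a higher rate than other tubes would leave fewer cases for sensitivity, lower the proportion of airway placements in the analysed set, and so pull PPV down and NPV up. Sensitivity, PPV and NPV are all listed outcomes.

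**Working it through.** **The plan's own figure.** With p = 0.90, margin d = 0.03 and two-sided 0.05, the simple normal formula n = z²p(1−p)/d² gives 385. Requiring both sides of the exact interval to lie within 3 points gives 492, close to the stated 500. At 500 the normal half-width is 2.63%. The product 39 × 13 = 507 is correct. The figure is therefore reproduced, but it holds only when all 500 enter the denominator concerned. For sensitivity, only airway placements do.

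**Inputs for the exclusion check.**

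- N = 507 (Data analysis).
- Sensitivity 0.96 and specificity 0.99: the pooled values in the Introduction.
- Airway prevalence 3%: assumed.
- Aspirate success 90% in non-airway tubes, and 30% to 90% in airway tubes: assumed. The protocol gives no prevalence for this population and no aspirate rate.

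**Nothing excluded.** Airway tubes: 507 × 0.03 = 15.2. Non-airway tubes: 491.8.

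- TP = 15.2 × 0.96 = 14.6; FN = 0.6
- FP = 491.8 × 0.01 = 4.9; TN = 486.9
- PPV = TP/(TP + FP) = 14.6/19.5 = 74.8%
- NPV = TN/(TN + FN) = 486.9/487.5 = 99.88%

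**After exclusion.** Multiply TP and FN by the airway aspirate success rate, and FP and TN by 0.90. FP becomes 4.43 and TN becomes 438.2.

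| Airway aspirate success | Airway cases left | TP | PPV | NPV |
|---|---|---|---|---|
| 30% | 4.6 | 4.38 | 49.7% | 99.96% |
| 50% | 7.6 | 7.30 | 62.3% | 99.93% |
| 70% | 10.6 | 10.22 | 69.8% | 99.90% |
| 80% | 12.2 | 11.68 | 72.5% | 99.89% |
| 90% (equal loss) | 13.7 | 13.14 | 74.8% | 99.88% |

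The effect on PPV runs from large to small as the gap in aspirate success closes, and it vanishes when loss is equal. The NPV shift is always upward but below 0.1 percentage point.

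**Sensitivity.** In every row TP and FN are scaled by the same factor, so expected sensitivity stays at 96%; likewise specificity stays at 99%. What changes is precision. Even with no false negatives, the exact 95% interval for sensitivity is 78% to 100% on 15 airway cases and 48% to 100% on 5.

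Expected sensitivity shifts only if loss among airway tubes also depends on the capnography result, for instance if a blocked tube gives both a false negative and no aspirate. As an illustration, losing 50% of true positives and 90% of false negatives gives 0.96 × 0.5/(0.96 × 0.5 + 0.04 × 0.1) = 0.48/0.484 = 99.2%.

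**The case against.** The strongest reply is that the protocol need not be read this way. The Reference standard section makes radiography the reference standard and adds pH as a further measurement, the 2×2 cells allow one or more reference tests, and the X-ray follows the pH step with no condition attached. On that reading an X-ray-only case has a reference result and stays in. This stands as a possible reading. It does not remove the problem, because the Abstract and the accuracy calculation both name the two tests together, and nothing says which reading governs a fixed exclusion rule.

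The second reply is that uneven loss is an assumption. This also stands. The Introduction lists aspirate failure as a general limitation, with no rate and no link to airway position, and a pH reading needs fluid but not necessarily gastric fluid. The mild rows of the table belong in the range as much as the steep ones.

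Three stronger readings are tempting and are not supported:

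- A reader might infer that the dropped tubes are mostly airway placements. Even at 30% airway success, the dropped tubes are 15.2 × 0.7 = 10.6 airway and 491.8 × 0.1 = 49.2 non-airway, so 49.2/59.8 = 82% are not in the airway. They may be enriched for airway placements, but they are not mainly such.
- A reader might infer that sensitivity and specificity are themselves biased. Loss that depends only on position leaves their expected values unchanged.
- A reader might infer that procedures stopped for respiratory intolerance are certainly lost. The stopping sentence comes after the description of the index test, and the next sentence arranges an X-ray, so both results may exist. If insertion itself was abandoned, there may be no placement to classify. The text does not settle which.

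**Conclusion.** The point holds in conditional form. The protocol fixes a complete-case rule and, on the literal reading of its combined reference, applies it to cases that the X-ray alone could classify. Under the stated assumptions (3% prevalence, 96% and 99% accuracy, 90% non-airway aspirate success), PPV falls from 75% to between about 50% and 73% as airway aspirate success runs from 30% to 80%, and the airway cases available for sensitivity fall from about 15 to between about 5 and 12. NPV rises slightly. None of this occurs if aspirate failure is equally common in both groups, apart from a proportionate loss of cases. The protocol does not show that failure is uneven, so the size is a range and not an estimate. The loss is avoidable in any scenario, which is why the rule merits a change before the data are seen.

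**What to change.** Amend the missing-data sentence in Data analysis to say that a case enters the accuracy analysis whenever the index test and the X-ray are both available, that airway status is taken from the X-ray location already recorded under Data collection, and that a missing pH does not exclude the case. Bring the Abstract, the Reference standard section and the accuracy calculation into line with that statement.

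In the participant flow, report no-aspirate cases and stopped procedures by index result. Where a placement has an index result but no X-ray, add one bounding analysis that scores it first as airway and then as non-airway.

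The cost is a short rewording and one extra table. It needs no new data and no change to patient care.

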Despite the potential benefits, some gaps regarding the use of ETCO_2_ detection were identified in the literature. First, the majority of included studies in the two meta-analyses examined critically ill patients or patients with mechanical ventilation [16,17]. Also, the two studies in Hong Kong were conducted among a small sample of hospital patients and community-dwelling older adults. Thus, there is limited evidence on the diagnostic accuracy of ETCO_2_ detection in acute and rehabilitation settings, particularly general wards, accident and emergency departments (AEDs) and intensive care units (ICUs). Second, the sensitivity and specificity of ETCO_2_ detection shown in the meta-analyses were less than 100%. Factors such as recent ingestion of carbonated fluids or poor connection between NGTs and ETCO_2_ detectors may result in false positive or false negative results [16,17,19]. Therefore, further examination of strategies to enhance the diagnostic accuracy of ETCO_2_ detection is needed. A protocol on the procedure of carrying out ETCO_2_ detection is also needed to avoid the possibility of false results caused by mal operation of the device or tubing misconnections. Third, ETCO_2_ detection is suggested to be effective only in differentiating between respiratory and GI placement of the NGTs. The use of this method to verify correct tube placement in the stomach, either alone or in combination with other index tests or reference standards, is yet to be determined. Thus, this study aims to discern the diagnostic accuracy of ETCO_2_ detection using capnography in verifying the correct placement of NGTs among adult patients in hospital settings.

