## Discussion

This study is aimed at determining the diagnostic accuracy of ETCO_2_ detection using capnography in verifying the correct placement of NGTs among adult patients in hospital settings. Ensuring the correct placement of NGTs is a necessary and important step to ensure patient safety. Despite the various methods examined in literature for verifying NGT placement, the diagnostic accuracy of these methods is still suboptimal and often compromised by different patient- or equipment-related factors such as availability of aspirates or conditions of the test devices [7,16,17]. This study will provide evidence on the diagnostic accuracy of capnography in verifying NGT placement, and its applicability to patients in hospitals settings, evidence of which is limited in the current literature.

In this study, capnography will be examined in combination with the reference standards, including radiography and testing for pH values in gastric aspirates. This examination approach will identify the optimal combination of test results in verifying the correct placement of NGTs. A multicenter, observational trial of 85 patients undergoing general anaesthesia, orotracheal intubation and mechanical ventilation has suggested using a ETCO_2_ cutoff value of 25.5 mmHg for NGT tracheal misplacement and a pH cutoff value of 4.25 for NGT correct gastric placement for achieving a higher level of accuracy in determining gastric placement of NGTs [27]. Indeed, given that the use of ETCO_2_ may be limited in merely differentiating between tracheal and GI placement of NGTs, the use of more than one index test could be superior in increasing the diagnostic accuracy. This study will help determine a fast and effective method for detecting NGT placement in the respiratory tract, which is crucial to preventing respiratory complications associated with misplaced NGTs. Furthermore, an algorithm illustrating the decision making based on the results of these tests can be developed to guide practice. The results of this study will also inform the update of clinical practice guidelines regarding the recommendations across the Hospital Authority Hong Kong in verifying NGT placements in acute and rehabilitative settings.

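### The complete-case rule drops capnography attempts that give no valid result, so reported accuracy may be more favourable than accuracy over all attempts; the size is unknown

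*Protocol article*

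**What the plan says.** The Data analysis section fixes the handling of missing results: "Any cases with missing data on the index test or the reference standard results will be excluded from the test accuracy analysis". It then defines true and false positives and negatives and computes sensitivity, specificity and predictive values from those four cells. The table has no cell for an attempt without a result.

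Other sections bear on how often this could happen and how it would be recorded:

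- **Index test** gives a two-way rule. A waveform, or an ETCO2 value above the cut-off, means airway placement; anything else that is read is a negative. (The abstract and this section give different cut-offs, which must be reconciled, but nothing here depends on which applies.)
- **Introduction** says that "poor connection between NGTs and ETCO_2_ detectors may result in false positive or false negative results".
- **Discussion** says that methods of verification are often compromised by "patient- or equipment-related factors such as availability of aspirates or conditions of the test devices".
- **Data collection** records "the number of index tests performed per participant", so repeat tests are foreseen.
- **Procedures** requires a device check before insertion, an air flush before the reading, and a minimum reading time.

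The abstract and Discussion say that the results should inform decisions on adopting capnography routinely.

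**The concern.** A ward that attempts capnography and obtains no valid reading has not verified the tube. For a decision on routine use, that attempt is information about the test. The exclusion rule treats it like a form that was never filled in.

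The rule then answers a narrower question than the adoption decision poses: how accurate capnography is when it can be read, rather than how often an attempt gives the right answer. On the second measure, with no-results counted as incorrect, the complete-case figure can be equal or higher but never lower.

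Sensitivity is the more exposed measure if airway placements are few, because one or two unreadable airway cases can then move it by several points.

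The point concerns the index-test half of the rule only. Missing X-ray or pH results are a different problem.

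**Working it through.** **1. The plan's own figure.** The article expects both measures to exceed 90% and holds that "a sample size of at least 500 participants would be sufficient to estimate these parameters". The stated precision is 3 percentage points either way, with alpha 0.05. At p = 0.90:

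- Wald: n = 1.96² × 0.90 × 0.10 / 0.03² = 384.1, so 385.
- Clopper–Pearson, lower arm no more than 3 points: n = 492.
- At n = 500 the Clopper–Pearson interval is 87.0% to 92.5%, with arms of 2.97 and 2.49 points.

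The stated 500 is therefore reproduced, taking all participants as the denominator of each measure, as the article does. The target is 39 × 13 = 507, which leaves 7 spare (7/507 = 1.4%).

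**2. Is lost precision the problem?** No. If an assumed 5% or 10% of 507 are excluded, 482 or 456 remain. The Clopper–Pearson lower arm is then 3.03 or 3.13 points, against 2.95 at 507.

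**3. Effect on the estimates.** Take one reference-standard group with n attempts, of which m have no valid result and c are correct. The complete-case value is c/(n − m). With no-results counted as incorrect it is c/n. Since c/n = c/(n − m) × (1 − m/n), the second equals the first times (1 − f), with f = m/n in that group.

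Inputs: sensitivity 0.96 and specificity 0.99, the updated pooled values in the Introduction. The failure rate f is not given; 1% to 10% is assumed.

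| f (assumed) | Sensitivity 0.96 becomes | Specificity 0.99 becomes |
|---|---|---|
| 1% | 0.9504 | 0.9801 |
| 2% | 0.9408 | 0.9702 |
| 5% | 0.9120 | 0.9405 |
| 10% | 0.8640 | 0.8910 |

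**4. Small numbers of airway placements.** The number expected is not given. Assumed cases:

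- 10 airway placements, 1 with no result, the other 9 detected: 9/9 = 100% (95% CI 66.4–100) against 9/10 = 90% (55.5–99.7).
- 25 airway placements, 2 with no result, 22 of the other 23 detected: 22/23 = 95.7% against 22/25 = 88.0%.
- 497 non-airway placements, 10 with no result, 482 of the other 487 negative: 482/487 = 99.0% against 482/497 = 97.0%.

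**5. The same events recorded as flat traces.** Under the Index test rule a flat trace is a negative. The single airway failure then gives 9/10 = 90% under the plan's own analysis. The ten non-airway failures give (482 + 10)/497 = 99.0%. In general, at f = 5%, sensitivity is 0.96 × 0.95 = 0.912 and specificity is 0.99 × 0.95 + 0.05 = 0.9905. Nothing is lost from the table in this case. The effect in steps 3 and 4 arises only for attempts recorded as having no result.

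**The case against.** The strongest reply is that the rule speaks of missing data and does not say that a device fault or an uninterpretable trace is coded as missing. Step 5 shows how much depends on that. A reader might infer that capnography's failures in general vanish from the analysis. The documents do not support this: a blocked or loose line showing no waveform and a low value is a counted negative, and the Introduction describes poor connection as producing false results, which are also counted. The Discussion remark concerns methods in the literature generally and names aspirates; it does not predict absent capnography readings. This part of the reply stands and confines the point to attempts recorded as no result.

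Second, such attempts may be rare. Nurses are trained, tested and observed, the device is checked, the tube is flushed, and the pilot study reviews completeness and usability. The instruction to stop on respiratory intolerance appears with the pH step, after the index test, so it does not clearly create missing capnography results. This also stands, but it bears on how often no-results occur, not on how they are handled.

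Third, accuracy among valid results is a recognised quantity, and counting every no-result as wrong is a worst-case convention. Agreed; hence the complete-case estimate should stay.

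Fourth, a table of inconclusive results might be left to a fuller document. That would answer a complaint about silence. Here the article itself fixes the exclusion and a four-cell table without distinguishing the two kinds of missing result.

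**Conclusion.** The point holds in a limited form. The stated rule removes any attempt recorded as having no capnography result and does not distinguish it from a test that was never done. Accuracy among readable tests may therefore be more favourable than accuracy among all attempts.

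The size cannot be fixed from the document. The ranges shown rest on three assumptions: a failure rate of 1% to 10%, the pooled values as the complete-case result, and every no-result counted as an error. The small-number examples also assume the count of airway placements.

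Two stronger conclusions are not supported. One is that the study's accuracy figures are overstated as a matter of fact: if no-results are few, or arise for reasons unrelated to tube position and to the reading that would have been obtained, sensitivity and specificity among valid tests are not biased. The other is that only the first index test may be scored. The article records how many tests were done, but that requirement does not follow from the exclusion rule.

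**What to change.** Keep the complete-case estimate and amend the index-test part of the rule:

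1. Record capnography not done and capnography attempted with no valid result as separate categories, and state that a flat or low trace is a negative, as the Index test section implies.
2. Report the no-result rate by reference-standard status in a 3×2 table (positive, negative, no valid result).
3. Add a sensitivity analysis of sensitivity and specificity in which attempted no-results count as incorrect, labelled as a worst case.

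The cost is a coding item on the data collection form if it lacks one, a few lines of analysis text, one extra table, and possibly less favourable secondary figures. No change to the sample size or to any clinical procedure is needed.
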